#### Secondary/exploratory outcomes

Secondary outcomes will be tested using a complete-case ITT population, including all participants for whom data are available at the post-intervention timepoint (irrespective of whether they completed the intervention or not). To test for changes in motor consolidation, we will determine the difference in performance from the end of evening training relative to the morning retest on the GripAble motor learning task at each time point. To determine whether motor consolidation improves for the dCBT group compared with control, we will use an ANCOVA. The model will test for between-group differences at post-intervention (~10 weeks following randomisation), with baseline consolidation score as a covariate. Changes in actigraphy-derived sleep measures will also be analysed using an ANCOVA, testing for differences between groups at 10 weeks following randomisation with baseline scores added as covariates. To explore whether the magnitude of changes in sleep measures relate to changes in motor consolidation, we will use correlational analysis (either Spearman’s or Pearson’s correlations as appropriate), testing for associations between changes in SCI and actigraphy-derived sleep measures (estimated total sleep time, WASO and sleep fragmentation index) with changes in motor consolidation. Changes in symptoms of depression and fatigue in the dCBT group compared with the control group will also be analysed using an ANCOVA to examine differences between groups on the PHQ-9 and FSS at follow-up, with baseline score added as a covariate. For all analyses, we will include covariates such as age, sex, time since stroke, etc as required.

### Patient and public involvement

A patient and public involvement (PPI) contributor (RF) has been involved in the setup of the study, including providing feedback on the dCBT programme and assisting in interviewing/appointing the research assistant who will be responsible for day-to-day management of the study. They have critically reviewed the protocol and will be included as a co-author in all published material from this study.

Throughout our previous studies of sleep after stroke and brain injury, we have discussed sleep concerns with patients in hospital and in the community (eg, at stroke user group meetings and stroke awareness day events). We have encouraged patients to try out and provide feedback on the motor learning task at various public/patient engagement events before and throughout the design of the study. We used this feedback to design the instructions we give to participants and to decide on which level of difficulty would be appropriate. Stroke survivors have also been involved in reviewing participant facing documents but will not be directly involved in recruitment of study participants or conduct of the study. We will seek further assistance from PPI contributors to help with preparation of lay summaries and dissemination of our results to ensure that these are meaningfully communicated to the stroke community.

### Study monitoring

Regular monitoring of participants will be performed by the research team as appropriate. Data will be evaluated for compliance with the protocol and accuracy in relation to source documents. The study may also be monitored or audited by responsible individuals from the University Sponsor and the NHS Trust(s).

At 10 weeks following randomisation, we will check with participants for the potential occurrence of any adverse effects. Any adverse events (AEs) that occur during enrolment in the trial will be documented and participants will be advised on the best course of action. This may include withdrawing from certain assessments or contacting their general practitioner. Expected minor AEs include: mild skin irritation due to wearing the actigraphy monitor, tiredness/worsening of sleep as part of the sleep restriction included in the dCBT programme, minor distress caused by completing sleep and mood questionnaires, etc.

There are no anticipated serious AEs (SAEs) associated with this trial. Any SAEs that occur will be reported to the appropriate research ethics committee, where in the opinion of the chief investigator the event was ‘related’ (resulted from administration of any of the research procedures) and ‘unexpected’ in relation to those procedures. Reports of related and unexpected SAEs will be submitted within 15 working days of the chief investigator becoming aware of the event, using the Health Research Authority (HRA) report of SAE form (see HRA website).

### Data management

Access will be granted to authorised representatives from the sponsor and host institution for monitoring and/or audit of the study. The participant will be referred to by their study ID, not by name, on all documents apart from the consent form. All trial data will be entered on paper and/or an electronic document (eg, Microsoft Excel) and stored safely in confidential conditions.

### Early discontinuation/withdrawal

During the trial, a participant may choose to withdraw early at any time. In addition, an investigator may discontinue a participant from the trial if considered necessary for any reason including, but not limited to: ineligibility (either arising during the study or retrospectively having been overlooked at screening), significant protocol deviation, *s*ignificant non-compliance with study requirements, medical instability and subsequent stroke affecting motor function or requiring readmission. The type of withdrawal and reason for withdrawal will be recorded. If permitted and appropriate, data obtained up until the point of withdrawal to be retained for use in the study analysis. No further data or samples would be collected after withdrawal. Withdrawn participants will be replaced providing there is sufficient time to conduct all follow-up assessments within the study period.

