#### Sample size distribution

Based on prior work in our lab comparing dCBT with sleep hygiene information in stroke survivors^36^ and other studies involving dCBT in people who suffer from insomnia, we estimate a medium between group effect size of d=0.7. In order to achieve this, a sample size of n=76 will be required (α=0.05, power=80%, 2:1 random allocation ratio dCBT:control, two-tailed independent samples t-test). A sample size of n=100 was selected to accommodate an approximate 25% dropout rate (determined from previous research experience). As the at-home motor training component of the trial is optional, we expect the resultant sample size to be reduced.

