### Post-intervention

Approximately 10 weeks following randomisation, assessments of sleep (SCI, 7-night actigraphy, sleep diary), mood (PHQ-9), fatigue (FSS) and motor consolidation (GripAble task) will be repeated. Participants will be randomly assigned a different level of motor learning task, so that the movement pattern is different to that which they learnt at baseline. Any participants who have not completed the dCBT programme by 10 weeks (or do not wish to complete it) will still be given the opportunity to complete the post-intervention assessments. Once completed, any equipment will be picked up by a researcher or return postage organised (dependent on participant preference, location and desire to complete voluntary training, see next section).

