### Data analysis

#### Primary outcome

The primary outcome, SCI score at post-intervention, will be analysed using intention-to-treat (ITT). An analysis of covariance (ANCOVA) will be used to test whether self-reported symptoms of insomnia are improved for the dCBT group in comparison to the control group. The model will test for differences in SCI scores between groups at the post-intervention time point (~10 weeks following randomisation), with baseline score, sex and time since stroke added as covariates. All ANCOVAs will be run in general linear model format.

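### The withdrawal rule lets unblinded staff end outcome collection for randomised participants and replace them, which could undermine the intention-to-treat primary analysis

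*Protocol article*

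**What the plan says.** The rule is in the protocol article, Early discontinuation/withdrawal. Besides a participant's own choice to leave, "an investigator may discontinue a participant from the trial if considered necessary for any reason". The examples listed are ineligibility (including ineligibility missed at screening), significant protocol deviation, and significant "non-compliance with study requirements, medical instability and subsequent stroke affecting motor function" or requiring readmission. The section then says "No further data or samples would be collected after withdrawal. Withdrawn participants will be replaced", on condition that enough time remains for the replacement's follow-up. Data gathered before withdrawal are kept where permitted and appropriate, and the type of and reason for withdrawal are recorded.

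Four other sections bear on this:

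- **Primary outcome (Data analysis):** "The primary outcome, SCI score at post-intervention, will be analysed using intention-to-treat (ITT").
- **Post-intervention:** participants who have not finished dCBT by 10 weeks, or do not wish to, "will still be given the opportunity to complete the post-intervention assessments".
- **Randomisation and blinding:** randomisation follows the baseline assessments. Neither participants nor the staff running the study day to day are blinded.
- **Sample size distribution:** "A sample size of n=100 was selected to accommodate an approximate 25% dropout rate".

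**The concern.** Discontinuation here is from the trial, not only from the programme, and it can be the investigator's decision while the participant is still willing to answer a questionnaire. Because randomisation comes after baseline, everyone discontinued later is a randomised participant. Because the SCI is taken only at baseline and at about 10 weeks, a participant removed before week 10 contributes no post-randomisation value of the primary outcome. No later analysis plan can recover an outcome that was never collected. Any imputation would rest on baseline data and on untestable assumptions about people selected for the way they behaved in the trial.

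The opportunity for removal is not the same in the two arms. The dCBT arm has six sessions, weekly videos and a daily online diary; the control arm has no research intervention. Non-compliance with the programme can therefore arise only in the dCBT arm, and the people judging it know the allocation. If those removed would have benefited less or done worse, the participants who remain make dCBT look better than it is. Recruiting a replacement restores the head count but not the randomised comparison.

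**Working it through.** **1. The plan's own sample size.** Inputs (Sample size distribution): d = 0.7, two-sided α = 0.05, 80% power, 2:1 allocation, t-test. The normal approximation gives 25 controls and 75 in total. By the noncentral t, 50 + 25 = 75 has power 0.805 and 51 + 25 = 76 has power 0.808. The stated 76 reproduces. For dropout, 76 / 0.75 = 101.3, or 102 when rounded up, and 100 × 0.75 = 75. The stated 100 is within rounding of an approximate 25% allowance. The sample size is not in dispute, and it already allows for the loss that replacement would also make up.

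**2. The sections side by side.** Consider a dCBT participant who stops using the programme in week 3. Under Post-intervention, that person is still offered the 10-week SCI. Under Early discontinuation/withdrawal, the same person may be discontinued for significant non-compliance and would then have no 10-week SCI. The article does not say which section governs, so the outcome's existence can depend on an unblinded judgement.

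**3. Size if there is a true effect.** The article gives no rate of investigator discontinuation, so the share p of the dCBT arm removed is an assumption. The upper value, 25%, equals the whole planned dropout. Suppose those removed get no benefit, those retained show d = 0.70, and the analysis uses observed outcomes only. The effect over all randomised is then 0.70 × (1 − p), and the overstatement is 1/(1 − p) − 1.

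| p | effect over all randomised | shown | overstatement |
|---|---|---|---|
| 0.10 | 0.63 | 0.70 | 11% |
| 0.15 | 0.595 | 0.70 | 18% |
| 0.25 | 0.525 | 0.70 | 33% |

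The result depends on the zero-benefit assumption. Now fix the effect over all randomised at 0.7 and let those removed have effect e, so that the retained show (0.7 − p·e)/(1 − p). With half benefit (e = 0.35) this is 0.74 at p = 0.10 and 0.82 at p = 0.25. With full benefit (e = 0.7) it is 0.70, and there is no bias.

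**4. Size if there is no true effect.** Let m be the gap in outcome, in SD, by which those removed would have scored worse than those retained, whatever their treatment. The retained dCBT mean is then shifted by p × m. Take n1 = 67(1 − p) against n2 = 33 (100 split 2:1), no control removals and an unadjusted two-sided 5% t-test. Rejection rates from the noncentral t are:

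| p | m | bias p × m (SD) | rejection rate |
|---|---|---|---|
| 0.10 | 0.3 | 0.03 | 5.2% |
| 0.10 | 0.5 | 0.05 | 5.6% |
| 0.25 | 0.5 | 0.125 | 8.5% |
| 0.25 | 0.8 | 0.20 | 14.3% |

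If those removed would have done better (m = −0.3), the bias is −0.03 SD at p = 0.10 and −0.075 SD at p = 0.25, against dCBT.

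**The case against.** The strongest reply is that the article already protects the group at issue. Post-intervention offers follow-up to dCBT non-completers, and the secondary analysis set includes people whether or not they completed the intervention. On that reading, stopping dCBT is not withdrawal, and the withdrawal section concerns people who leave the trial altogether. Recording the type of withdrawal suggests that such distinctions exist, and the full protocol may define them. This softens the concern but does not remove it: the withdrawal section names non-compliance as a ground for ending participation, without limit or cross-reference.

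Several stronger readings are tempting, and the article does not support them:

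- **That the primary analysis cannot be ITT.** Nothing excludes withdrawn or replaced participants from the primary set, and data before withdrawal are kept where permitted. They can stay in the set with a missing outcome, handled by a method that may be in the unseen analysis plan. The secondary set is called complete-case and the primary set is not, so a complete-case primary analysis should not be presumed.
- **That the result will favour dCBT.** This is the likely direction, but step 3 gives zero bias and step 4 a reversed bias under other assumptions.
- **That the rule acts only on the dCBT arm.** The ground is non-compliance with study requirements. Both arms have actigraphy, sleep diaries and the timed grip task, and the other listed grounds belong to neither arm.
- **That replacement breaks the limit of 100 or invalidates power.** Replacement depends on time remaining. The article does not say whether replacements count towards that limit, and the sample size reproduces.

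The arithmetic is also open to challenge. It puts all removals in one arm, and its upper end treats the entire planned dropout as selective. It is unadjusted, whereas the planned model is fitted "with baseline score, sex and time since stroke added as covariates", which would absorb any part of the gap that those covariates explain. It does not model the replacements. These points stand, so the figures are illustrations and not predictions.

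**Conclusion.** The concern holds as a stated rule that permits avoidable, possibly arm-differential loss of the primary outcome. It does not hold as proof that the ITT analysis is impossible or that the trial is biased towards dCBT.

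The sizes in steps 3 and 4 rest on assumed removal of 10–25% in the dCBT arm alone, on analysis of observed outcomes, and on either no benefit among those removed or a prognostic gap of 0.3–0.8 SD. At the low end the distortion of the test is negligible; at the high end it is not. The case for acting does not depend on the high end. The Post-intervention, Primary outcome and Early discontinuation/withdrawal sections need reconciling in any case, and an uncollected 10-week SCI cannot be obtained later.

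**What to change.** Reconcile the three sections with wording to this effect:

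1. Distinguish stopping or not following the intervention from withdrawal of consent for data collection.
2. State that non-compliance, protocol deviation or ineligibility found later does not by itself end outcome collection.
3. Seek the 10-week SCI from every randomised participant who has not withdrawn consent for data.
4. Keep all randomised participants in the primary ITT set in their allocated arm. Count anyone recruited later as an additional participant, not a substitute, and say how such participants count towards the limit of 100.

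This concerns data collection and the analysis set only. It takes no position on who should stop dCBT. The cost is a wording amendment and a few more short questionnaires.

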### Ethics and dissemination

This study has received both Health Research Authority (HRA) and Health and Care Research Wales (HCRW) approval (IRAS ID: 306291). The study has also received approval from the National Research Ethics Service (22/EM/0080). The trial has been registered on a publicly accessible database prior to the recruitment of the first participant (clinicaltrials.gov). Results will be uploaded to clinicaltrials.gov within 12 months of the end of trial declaration by the CI or their delegate and disseminated via presentations at scientific conferences, peer-reviewed publication, public engagement events, stakeholder organisations and other forms of media where appropriate. The investigators will be involved in reviewing drafts of the manuscripts, abstracts, press releases and any other publications arising from the study.
